### Statistical analysis plan

All analyses will be conducted in accordance with intention-to-treat (ITT) principles, i.e. all randomized individuals will be included in the analysis [61]. In addition to the primary ITT analysis, per-protocol analysis will be conducted.

For the primary outcome, repeated measures mixed models (time*group interaction) will be conducted to test for differences in efficacy between the intervention groups. In case of statistically significant results, group differences will be investigated using post-hoc pairwise comparisons (Bonferroni correction). Secondary analyses using repeated measures mixed models will be performed on variables related to help-seeking behavior and depression stigma. In addition, repeated measures mixed models will be conducted to examine long-term group differences in PHQ-A scores at the six-month, one-year, and two-year follow-up timepoints, respectively. All analyses will include testing for interaction effects with study site (time*group*study site interaction).

Additionally, cost-effectiveness analyses and cost-utility analyses will be conducted. Cost-effectiveness analyses include the calculation of the ICER. The ICER indicates the additional cost for each additional (primary) outcome that has to be paid under routine care conditions. During these analyses, standard health economy techniques will be applied, such as bootstrapping techniques for estimating ICER variability, the calculation of cost-effectiveness acceptability curves (CEAC), and calculation of willingness-to-pay (WTP) criteria [62, 63]. In addition, a cost-utility study will be conducted that requires the transformation of longitudinal quality of life data (assessed with the KIDSCREEN-10) into preference measures, for the calculation of QALYs lost or gained during follow-up in order to calculate costs per QALY of the intervention.

Analyses will be performed using IBM SPSS Statistics and *p* values < 0.05 will be considered statistically significant.

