### Randomization

Following the school-based baseline screening within the ProHEAD consortium, participants eligible for the E.motion trial will receive an e-mail including information about the trial and access details for the baseline assessment within the E.motion trial. After completing this assessment, participants will be randomized with equal probability (in a 1:1:1 ratio) to one of the three intervention groups. The assignment to the three conditions will be randomized, stratified for gender and school type. Randomization will be conducted externally and follow a permutated block design. Following randomization, participants will be contacted again via e-mail to be informed about their allocation to the respective intervention group and receive access details for the specific online programs. Blinding is not possible as the study assistants will be involved in delivering the interventions. However, the risk of a potential bias is considered minimal as the study outcome variables are exclusively based on self-report. For all treatment arms, the intervention will be discontinued at any time for participants who withdraw consent to participate in the trial.

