### Outcomes and measures

#### Primary outcome

The primary outcome of the trial is depression symptomatology at the end of intervention as measured by the PHQ-A score. The depression module of the PHQ-A [32, 33] comprises nine items assessing depressive symptoms based on the diagnostic criteria for depression according to the fourth edition of the Diagnostic and Statistical Manual of Mental Disorders (DSM-IV) [48]. Respondents rate the frequency of the symptoms over the previous two weeks on a four-point Likert scale (0 = “not at all” to 3 = “nearly every day”). A sum score will be computed with higher scores indicating higher levels of depressive symptomatology. The PHQ-9 for adults has shown good reliability, validity, and sensitivity to change [49, 50].

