### Sample size calculation

We assume a small to medium effect (superiority of the two intervention groups over the control condition) on depressive symptomatology at postline after treatment as reported in meta-analyses on interventions for the prevention of depression in C&A [60]. Non-inferiority of the two active intervention groups is assumed. Repeated measures mixed models will be conducted (time*group interaction, alpha = 5%). Assuming a small to medium effect of *f* = 0.13, a lost-to-follow-up rate of 20%, and correlations of 0.2 among repeated measures, *n* = 363 individuals (*n* = 121 per group) need to be recruited for a test of the global hypothesis with 90% power. In case the ANOVA shows significant differences, post-hoc pairwise group comparisons can be conducted at a power of about 80% (Bonferroni correction) with the planned sample size.

Participants will be recruited within the ProHEAD consortium from the school-based sample of *N* = 15,000 screened C&A. Based on prevalence rates of approximately 5–12% of subthreshold depression in adolescents [14], 10% or *n* = 1500 of the screened C&A are expected to be eligible for inclusion in the trial. Thus, in order to meet the required sample size of *n* = 363, about 25% of eligible C&A would have to be willing to participate in the trial.

Criteria for the allocation of participants to the five individual ProHEAD trials are based on latest scientific evidence. However, this is the first time that the overall algorithm is applied on a consortium-wide basis simultaneously screening for various mental health problems. Therefore, an intermediate data analysis will be conducted following completion of 10% of the screening assessments (*N* = 1500) in order to determine the actual allocation ratio to the five ProHEAD trials and to adjust the screening algorithm if necessary.

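### The primary time-by-group test does not use the fact that baseline PHQ-A is equal in expectation; it is valid, but loses up to about 35% of the information that baseline adjustment would keep

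*Protocol article*

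**What the plan says.** The Primary outcome section defines a level at one time: "The primary outcome of the trial is depression symptomatology at the end of intervention as measured by the PHQ-A score". The Statistical analysis plan section tests it through an interaction: "For the primary outcome, repeated measures mixed models (time*group interaction) will be conducted to test for differences in efficacy between the intervention groups". Significant results are followed by Bonferroni-corrected pairwise comparisons. PHQ-A at six months, one year and two years is analysed separately, in additional models.

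The Sample size calculation section powers the same interaction at a 5% level: "Assuming a small to medium effect of *f* = 0.13, a lost-to-follow-up rate of 20%, and correlations of 0.2 among repeated measures", so that 363 "individuals (*n* = 121 per group) need to be recruited for a test of the global hypothesis with 90% power". It adds that "post-hoc pairwise group comparisons can be conducted at a power of about 80% (Bonferroni correction) with the planned sample size".

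Under Randomization, the trial's own baseline assessment is completed first, and then "participants will be randomized with equal probability (in a 1:1:1 ratio) to one of the three intervention groups". Eligibility was decided earlier, at the school screening, on a PHQ-A score of 5 to 9. The analysis section says that all randomised individuals are included. It names no baseline covariate and no constraint on the baseline means. No PHQ-A standard deviation is given anywhere.

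**The concern.** With baseline and end of intervention as the two times, an unconstrained time-by-group interaction compares changes from baseline. When the two scores are only weakly correlated, subtracting the baseline adds more noise than it removes. Because baseline is measured before randomisation, the three arms have the same expected baseline. Fitting a separate baseline mean per arm therefore spends precision on differences known to be zero in expectation.

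What is at stake is power, above all for the pairwise comparisons that decide whether either intervention beats the control website. Chance baseline imbalance also enters the estimated effect. At equal SDs it does so with weight 1 - 0.2 = 0.8, and it averages zero over randomisations.

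**Working it through.** **Inputs.** From the Sample size calculation: f = 0.13, correlation ρ = 0.2, alpha 0.05, N = 363 (121 per arm), 20% loss. Completers: 363 × 0.8 = 290, or 96.7 per arm. Assumptions: dropout completely at random, and equal SDs at both times, as the repeated-measures power formula implies. The equal-SD assumption is varied in step 5.

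**1. The plan's own figure.** For the interaction with m times, the noncentrality is λ = N·m·f²/(1-ρ), with (3-1)(m-1) and (N-3)(m-1) degrees of freedom. With m = 2, 90% power needs 303 completers (power 90.05%), and 303 × 1.2 = 363.6, which matches 363. With m = 3, 4 or 5 the interaction needs 246, 209 or 183, and none of these leads to 363. A between-group test averaged over four times also needs 303, but the plan names the interaction. The primary contrast is therefore baseline to end of intervention, without a baseline constraint.

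**2. Implied effect.** At m = 2 the formula corresponds to a between-arm SD of mean change of 2f = 0.26 end-score SDs. If both interventions are equally better than control by d, then 0.26 = d·√(2/9), so d = 0.55.

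**3. Variance of one arm's contribution** (end SD = 1):
- Interaction, completers only: 2(1-ρ)/96.7 = 1.60/96.7 = 0.01655.
- Interaction, mixed model on all randomised. Dropouts' baselines contribute, so the variance is (1-ρ²)/96.7 + (1-ρ)²/121 = 0.96/96.7 + 0.64/121 = 0.01522.
- Baseline-adjusted: (1-ρ²)/96.7 = 0.96/96.7 = 0.00993.

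The information loss against adjustment is 1 - 0.00993/0.01522 = 35% for the mixed model on everyone, and 1 - 0.96/1.60 = 40% on completers.

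**4. Power.** Global: λ = (2/3)d² divided by the variance above, 2 and about 287 df. Pairwise: d/√(2 × variance), noncentral t, two-sided 0.05/3.

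| Analysis | λ | Global power | Pairwise power at 0.05/3 |
|---|---|---|---|
| Interaction, completers only | 12.25 | 88.7% | 73% |
| Interaction, mixed model on all randomised | 13.32 | 91.2% | 77% |
| Baseline-adjusted | 20.42 | 98.6% | 93% |

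For the middle row the pairwise noncentrality is 0.5515/√(2 × 0.01522) = 3.16. If only the two comparisons with control were tested (0.05/2), the normal approximation gives Φ(3.16 - 2.24) = 82%.

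**5. Unequal SDs.** Let k be the baseline SD divided by the end SD. The mixed-model variance becomes 0.96/96.7 + (k-0.2)²/121.
- k = 0.75: 0.00993 + 0.3025/121 = 0.01243, a loss of 20%.
- k = 0.5: 0.00993 + 0.09/121 = 0.01067, a loss of 7%, with global power about 98%.

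The added term is a square, so asymptotically the unconstrained interaction is never more precise than the adjusted analysis.

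**The case against.** The strongest objection is that this is a preference and not a defect. The plan is consistent: it sizes the trial for the test it names, the figure of 363 reproduces, type I error is controlled and the estimate is unbiased. This stands, and it limits the point to efficiency. A reader might infer from the completer figures of 88.7% and 73% that the trial misses its promised power. The documents do not support that. The stated model includes all randomised individuals, and on that basis global power is about 91%. Pairwise power is about 77% or 82%, depending on whether three or two comparisons are corrected for, against a promise of about 80%.

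Second, a condensed article need not list every model term, and the recommended model is itself a repeated-measures mixed model with group-by-time terms. This stands in part: a fuller analysis plan could already contain the constraint. But the article does fix the interaction as the primary test and uses the unconstrained formula for its sample size, so the text as it stands points to the less precise analysis.

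Third, screening on PHQ-A 5 to 9 may narrow the baseline spread and shrink the loss. This also stands. The separate assessment before randomisation may widen the spread again, by an unknown amount. A reader might therefore take 40% as the loss. That figure needs both equal SDs and a completers-only analysis. A reader might likewise conclude that ignoring baseline altogether beats the planned test whenever the correlation is below 0.5. That too holds only with equal SDs: for change scores the condition is k above 2ρ, which is 0.4 here.

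**Conclusion.** The point holds as a loss of efficiency, not as an error, a bias or a shortfall in the stated global power. At ρ = 0.2, 20% loss and equal SDs, the planned interaction on all randomised participants gives up about 35% of the available information. Adjustment would raise global power from about 91% to 98.6%, and pairwise power at 0.05/3 from about 77% to 93%. The loss is about 20% or 7% if the baseline SD is 0.75 or 0.5 of the end SD. These figures assume dropout completely at random, and the power figures also assume both interventions equally better than control by 0.55 SD. The true SD ratio cannot be settled from the documents, but the direction can: adjustment does not lose precision asymptotically. The change is worth making, chiefly for the pairwise comparisons.

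**What to change.** State the primary contrasts as the differences between groups in PHQ-A at end of intervention. Estimate them from a constrained longitudinal mixed model: PHQ-A at the pre-randomisation assessment and at end of intervention as outcomes, one common baseline mean (no group main effect), terms for time and for group at end of intervention, and an unstructured covariance. This keeps participants who have a baseline but no end score, in line with the intention-to-treat statement, and can be fitted in the SPSS software already named. ANCOVA of the end score on baseline PHQ-A is the simple alternative, but it drops participants without an end score unless these are imputed. Use the same approach for the six-month, one-year and two-year PHQ-A analyses.

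The cost is a change of analysis wording: no new data, no new assessments and no more participants. It should be fixed before any outcome data are seen.

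### With three arms, Bonferroni behind a significant 5% global test is valid but not needed for family-wise control; testing each pair at 5% behind the same gate would gain about 5 to 9 points of power

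*Protocol article*

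**What the plan says.** The protocol article randomises 1:1:1 to three groups (Randomization). Under Statistical analysis plan, the primary outcome is tested with a repeated measures mixed model through the group-by-time interaction, and the next step is conditional: "In case of statistically significant results, group differences will be investigated using post-hoc pairwise comparisons (Bonferroni correction"). Under Sample size calculation the interaction test is set at 5%, with 363 participants (121 per group) for 90% power on the global hypothesis. The inputs are: "Assuming a small to medium effect of *f* = 0.13, a lost-to-follow-up rate of 20%, and correlations of 0.2 among repeated measures". If the global test is significant, "post-hoc pairwise group comparisons can be conducted at a power of about 80% (Bonferroni correction) with the planned sample size".

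On the expected pattern the same section says: "We assume a small to medium effect (superiority of the two intervention groups over the control condition"), and "Non-inferiority of the two active intervention groups is assumed". I read this as two interventions about equally better than control.

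Two things are not stated: the number by which Bonferroni divides, and the time points in the primary model. The six-month, one-year and two-year PHQ-A scores are described as additional analyses.

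**The concern.** The procedure protects against multiplicity twice: once by requiring a significant global test, and again by lowering the level of each pairwise test. With three groups the second layer is not needed for family-wise control.

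What is at stake is power for the comparisons that answer the trial's question. A significant global test does not say which intervention beats the control website; the pairwise comparisons do. Recruitment is also demanding: about 25% of the eligible adolescents would have to agree to take part. Power that costs no further participants is therefore worth having.

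**Working it through.** **Inputs.** From Sample size calculation: f = 0.13, ρ = 0.2, 20% loss, α = 5%, 121 per group. Assumptions: two measurements (m = 2, baseline and end of intervention), and the pattern control < intervention 1 = intervention 2 in benefit.

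**1. The protocol's sample size.** For the interaction test with k = 3 groups, λ = f²·N·m/(1−ρ), with df (k−1)(m−1) and (N−k)(m−1).
- N = 303: λ = 0.0169 × 303 × 2 / 0.8 = 12.80, df 2 and 300, power 90.0%.
- 303 × 1.2 = 363.6, which matches the stated 363. With three or five measurements the same route gives 296 or 220, so only m = 2 fits.
- With 20% loss, 121 × 0.8 = 96.8, or about 97 completers per arm, and global power is about 88.7%. I use 97 per arm, with 101 (303/3) as the upper case.

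**2. From f to a pairwise difference.** For means (0, d, d) the standard deviation of the means is d√2/3, so d = 0.13 × 3/√2 = 0.2758. On the change score the difference is 2d = 0.5515, the variance is 2(1−0.2) = 1.6, and the standardised difference is D = 0.5515/√1.6 = 0.436.

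**3. Why the gate is enough.** With three means, any two true pairwise nulls imply the third. Only two null situations exist:
- All three means are equal. No pair is tested unless the 5% global test is significant, so the error is at most 5%.
- Exactly one pair is equal. Only one false rejection is possible, and its test is at 5%.

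This argument does not depend on effect size.

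**4. Simulated family-wise error** (400,000 trials per scenario, 97 per arm, pooled variance):

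| Rule behind the 5% gate | All equal | One pair equal |
|---|---|---|
| 0.05/3 per pair | 4.2% | 1.7% |
| 0.05/2 per pair | 4.8% | 2.5% |
| 0.05 per pair | 5.0% | at most 5.0% |

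**5. Simulated power, counting the gate** (D = 0.436):

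| Rule behind the 5% gate | Each vs control, n = 97 | Each vs control, n = 101 | Both vs control, n = 97 |
|---|---|---|---|
| 0.05/3 per pair | 73.4% | 75.4% | 60% |
| 0.05/2 per pair | 77.4% | 79.3% | 66% |
| 0.05 per pair | 82.5% | 84.2% | 76% |

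As a check without the gate, the noncentrality at n = 97 is 0.436 × √48.5 = 3.04. The normal approximation gives 74.0%, 78.7% and 85.9% at the three levels, in line with the simulation.

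The gain is about 9 points over division by 3 and about 5 points over division by 2. Reaching the same power while keeping 0.05/3 would take about 118 completers per arm: (118 − 97) × 3 = 63 more.

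**6. Dependence on the pattern** (n = 97 unless stated).
- If f = 0.13 is the effect within a pair, power per comparison goes from 67–69% (0.05/3) to 77–79% (0.05) at 97 to 101 per arm.
- With the same f and equally spaced means, the weaker intervention against control goes only from 26% to 41%.

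**7. Dependence on the gate.** Suppose later follow-ups entered the global test and the arms differed only later. The gate would open although all arms were equal at end of intervention. With the gate fully open, three pairs at 5% have a family-wise error of 12.2%; Bonferroni by 3 holds it at 4.4%.

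**The case against.** The strongest defence is that the procedure is prespecified, conventional and valid. Bonferroni over the three pairs controls error whatever the global test contains, and step 7 shows that this robustness is real if the gate is loosely defined. This stands, and it is why the replacement sentence must name the time points.

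A reader might infer three stronger things that the article does not support.
- **That the plan tests at 0.05/3.** The divisor is not given. Division by 2, for each intervention against control, is possible. It shrinks the gain to about 5 points, and no error would then be spent on intervention 1 versus 2.
- **That the stated pairwise power of about 80% is wrong.** The sentence is worded as conditional on a significant ANOVA. Read that way with division by 3, power is 73.4/88.8 = about 83%. Division by 2 without conditioning gives 77.4% to 79.3%. Only division by 3 read unconditionally falls clearly short.
- **That dropping Bonferroni guarantees more than 80%.** It does so under the equal-benefit pattern only (step 6).

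The change is also not free. Simultaneous intervals are given up, and under the assumed pattern false rejection of intervention 1 versus 2 rises from 1.7% (0.05/3) to about 5%, which is still within the 5% family-wise limit.

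**Conclusion.** This is a cheap improvement, not an error. The plan is valid but conservative: no error rate is inflated and no statement in it is shown to be false. Behind the same gate, a 5% pairwise test rejects whenever the Bonferroni-corrected test does, and family-wise error stays at 5%. Power per comparison with control rises to about 83% from about 73% or 77%, depending on the unstated divisor.

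The error control rests on exactly three groups and on a 2-df global test of the same baseline-to-end-of-intervention change that the pairs compare. The power figures rest in addition on f = 0.13, ρ = 0.2, about 97 completers per arm and equal benefit of the two interventions.

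**What to change.** For the primary outcome, replace the Bonferroni step with a sentence such as:

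> If the 2-df global test of the group-by-time interaction from baseline to end of intervention is significant at 5%, each of the three pairwise comparisons of that same change is tested at the two-sided 5% level (closed test for three groups); the adjusted p-value of a pair is the larger of the global and the pairwise p-value.

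Add that later follow-ups do not enter this gate test. Bring the pairwise power statement under Sample size calculation into line, and say whether the figure is conditional on a significant global test.

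The change needs no further participants or data and should be made before outcomes are seen by arm. Its cost is that ordinary 95% confidence intervals for the pairs are not simultaneous and should be labelled so. If the sponsor prefers to keep Bonferroni, stating the divisor would be enough to make the rule definite.

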**Methods:**

The multicentre, randomized controlled E.motion trial is part of the German ProHEAD consortium (Promoting Help-seeking using E-technology for ADolescents). The objective of the trial is to investigate the efficacy and cost-effectiveness of two online interventions to reduce depressive symptomatology in high-risk children and adolescents with subsyndromal symptoms of depression in comparison to an active control group. Participants will be randomized to one of three conditions: (1) Intervention 1, a clinician-guided self-management program (iFightDepression®); (2) Intervention 2, a clinician-guided group chat intervention; and (3) Control intervention, a psycho-educational website on depressive symptoms. Interventions last six weeks. In total, *N* = 363 children and adolescents aged ≥ 12 years with Patient Health Questionnaire-9 modified for Adolescents (PHQ-A) scores in the range of 5–9 will be recruited at five study sites across Germany. Online questionnaires will be administered before onset of the intervention, at the end of the intervention, and at the six-month follow-up. Further, children and adolescents will participate in the baseline screening and the one- and two-year school-based follow-up assessments integrated in the ProHEAD consortium. The primary endpoint is depression symptomatology at the end of intervention as measured by the PHQ-A score. Secondary outcomes include depression symptomatology at all follow-ups, help-seeking attitudes, and actual face-to-face help-seeking, adherence to and satisfaction with the interventions, depression stigma, and utilization and cost of interventions.

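### The plan provides for comparing each intervention with control on the primary outcome only if the global test is significant, so a null global test leaves no planned efficacy estimate or interval for either intervention

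*Protocol article*

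**What the plan says.** The abstract of the protocol article states the aim: "The objective of the trial is to investigate the efficacy and cost-effectiveness of two online interventions to reduce depressive symptomatology", with an active control as comparator. The quantities of interest are therefore iFightDepression (iFD) minus control and group chat minus control.

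The statistical analysis plan section sets the primary analysis: "For the primary outcome, repeated measures mixed models (time*group interaction) will be conducted to test for differences in efficacy between the intervention groups". It continues: "In case of statistically significant results, group differences will be investigated using post-hoc pairwise comparisons (Bonferroni correction").

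The sample size section carries the same condition and attaches a power to it: "In case the ANOVA shows significant differences, post-hoc pairwise group comparisons can be conducted at a power of about 80% (Bonferroni correction"). The number of comparisons covered by the correction is not given.

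The cost-effectiveness analysis has no such condition. The secondary outcomes section defines the ICER as a cost difference divided by an outcome difference, and the statistical analysis plan section plans it whatever the efficacy result.

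**The concern.** A three-group interaction test with two numerator degrees of freedom says whether the groups differ somewhere. It does not say by how much either intervention differs from control, which is what the objective asks. The contrasts that do answer it are labelled post hoc and are planned only after a significant global result. The wording sets the condition on whether group differences are investigated, not merely on whether they may be called significant.

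At stake is what can be read from a null result. Without a planned interval for each contrast, a trial that has ruled out the effect it was designed for looks the same as one that is too imprecise to say. The plan is also uneven: after a null global test the economic analysis must still form an outcome difference, while the efficacy analysis plans none.

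**Working it through.** **Inputs from the sample size section.** Global test: "Repeated measures mixed models will be conducted (time*group interaction, alpha = 5"%). Effect: "Assuming a small to medium effect of *f* = 0.13". Further: "a lost-to-follow-up rate of 20%, and correlations of 0.2 among repeated measures". Also 90% power, 363 recruited, 121 per group. Allocation is 1:1:1 (Randomization section).

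**Assumptions.** Two time points (baseline and end of intervention), both interventions equally better than control, two-sided pairwise tests, and outcome SD 1 at each time point.

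**1. Reproducing the stated sample size.** For the interaction in a repeated-measures ANOVA with m = 2 time points, the noncentrality is λ = f²·N·m/(1 − ρ), with 2 and N − 3 degrees of freedom.
- N = 303: λ = 0.0169 × 303 × 2/0.8 = 12.80, power 0.900.
- 303 × 1.2 = 363.6, which matches the stated 363.
- With 20% lost, 363 × 0.8 ≈ 290 remain. Taking 97 per arm (291), λ = 12.29 and power is 0.888.

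**2. The effect behind that power.** With changes (d, d, 0), f = d/√18, so d = 0.13 × √18 = 0.55 SD. The variance of a change score is 2(1 − 0.2) = 1.6.

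**3. How often no contrast is planned.** Probability of a non-significant global test with 97 per arm (400,000 simulated trials per scenario):

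| True effect, both arms | Global test not significant |
|---|---|
| 0.55 SD (design effect) | 11% |
| 0.41 SD (75% of it) | 36% |
| 0.28 SD (50% of it) | 68% |

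**4. Whether the condition protects the error rate.** Under no difference anywhere, with no global test in front, the probability of any false claim is:
- three pairwise comparisons, Bonferroni over 3: 0.044;
- two comparisons with control, Bonferroni over 2: 0.046.

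Both are below 0.05 without the condition.

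**5. Whether the condition costs significant findings.** Power per contrast with control at 0.55 SD is 0.734 without the condition and 0.733 with it (Bonferroni over 3), or 0.783 and 0.774 (over 2). In 0.2% (over 3) or 1.7% (over 2) of all trials the condition blocks a contrast that would otherwise be significant. At 50 to 75% of the design effect this is about 0.5% or 4%.

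**6. What an interval would add after a null result.** The 95% half-width for one contrast is 1.96 × √(2 × 1.6/97) = 0.356 SD. Among simulated trials with a non-significant global test, the interval for a given intervention lies wholly below 0.55 SD in 87% if neither intervention works, and in 45% if the true effect of both is 0.28 SD. So the interval would often show that the design effect has been excluded.

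**The case against.** The strongest reply is that this is an ordinary testing hierarchy: an overall test, then corrected pairwise tests. Nothing in the article says that estimates or intervals will be withheld after a null result, the fitted model yields the contrasts in any case, and the layout of results is commonly left to a fuller document. Part of this stands. A reader might infer that a null trial gives no answer at all on either intervention. The article does not support that, because it does not forbid reporting the contrasts and it plans the ICER unconditionally. But the article is not silent here: it states a condition in two places, and an analysis plan that follows it would carry the condition forward.

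A reader might also infer that the rule inflates the published effects. Estimates read only after a significant global test are on average too large, by 6% at the design effect, 21% at 75% of it and 58% at half of it. That comes from selecting on significance, not from the estimator. A trial that passes the global test would report the same number with or without the condition, so removing it would not change these figures. Nor is the ICER biased by the rule, since it is not conditional on the test.

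Finally, 11% is simply the type II error of the design. The 36% and 68% rest on effects smaller than the one that reproduces the sample size, and belong mainly to a discussion of power. That is fair, and they are given only to show how the frequency grows.

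**Conclusion.** The point holds as one about estimation. The two sections agree in planning pairwise group differences on the primary outcome only after a significant global test, although the objective is the efficacy of each of two interventions against control. At the design effect about 11% of trials would end with no planned efficacy contrast or interval; the share rises if the true effect is smaller. An interval of about ±0.36 SD would often separate an informative null result from an inconclusive one. The condition adds nothing needed for error control and removes few significant findings, so little is lost in testing.

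The figures rest on two time points, 97 completers per arm, equal benefit in both intervention arms and two-sided tests. The familywise error and blocked-finding figures are given for two and for three comparisons because the article does not say which is meant.

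**What to change.** Add to the statistical analysis plan section: the iFD-minus-control and chat-minus-control differences in PHQ-A at end of intervention will always be estimated from the primary model and reported with 95% confidence intervals, whatever the global test shows; the global test and the Bonferroni correction govern only whether a difference is declared significant. Align the corresponding sentence in the sample size section.

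The cost is one sentence in the plan and two lines in the results table. It needs no extra participants and leaves the error rate for significance claims unchanged.
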